## Abstract

Because of the serious consequences of eating disorders on young women’s lives and because of the lack of specialised care facilities, assessing and implementing evidence-based prevention interventions is necessary. Switzerland, like other Western countries, has high prevalence rates of eating disorders. However, no prevention interventions have been evaluated in this country so far. This paper presents the protocol of a preliminary study with the aim to evaluate the acceptability and effectiveness of two interventions, the Body Project (BP) and the Healthy Weight Program (HW), for female students from French-speaking Switzerland. These two interventions were chosen because they have been widely evaluated and they proved to be effective in various countries. They take place in groups and include four weekly sessions over one month. Because of the pandemic situation, the group sessions will take place online on an collaborative platform. The design is a three-arm randomised controlled study. Ninety female students aged 18–25 and presenting with at least moderate body dissatisfaction will be randomised into three groups: (1) one-month BP intervention, (2) one-month HW intervention, and (3) one-month waiting-list control group followed by the BP intervention. Assessments of body dissatisfaction, thin-ideal internalisation, dietary restraint, negative affect, and eating disorder psychopathology will be conducted before and after the interventions or waiting list and after a one-month follow-up. ANCOVA and ANOVA with repeated measures will be used to assess group differences and follow-up stability. Acceptability will be assessed with a questionnaire on participants’ satisfaction with the interventions, group discussion at the end of the intervention, and with participants’ rate of attendance to the group sessions. The study results will provide additional data on these two eating disorders prevention interventions and will suggest ways for their dissemination and further evaluation in Switzerland.

## Introduction

Eating disorders are serious mental illnesses with severe consequences on the somatic, psychological, and social levels [1,2]. The diagnoses described in the current version of the Diagnostic and Statistical Manual of Mental Disorders (DSM-5 [3]) include three main disorders: 1) anorexia nervosa, which is characterised by severe dietary restriction and a weight below a healthy body mass index (BMI); 2) bulimia nervosa, which is characterised by episodes of compulsive eating and compensatory behaviours for weight control; and 3) binge eating disorder, which also includes compulsive eating episodes but without compensatory behaviours. Sub-threshold forms of these disorders, manifesting with only some symptoms of the full syndromes, also cause significant suffering [4]. An epidemiological study has shown that, in Switzerland, the lifetime prevalence rates of these disorders, calculated by adding lifetime prevalence estimates for anorexia nervosa, bulimia nervosa, binge eating disorder, any eating disorder, sub-threshold binge eating disorder and any binge eating, were 17.5% for women and 7.8% for men [5]. According to the authors of this study, these prevalences were comparable to those of other westernised countries and even higher for bulimia nervosa, which is a pathology strongly influenced by culture [6].

Mental disorders frequently develop in adolescents or young adults, and interfere with the developmental tasks required during these periods [7]. These disorders are likely to become established in adulthood, which is why public health initiatives aimed at youth can greatly contribute to the health of the community [7]. Regarding the field of eating disorders more specifically, people with eating disorders often feel ashamed of their disorder, which prevents them from seeking help [8]. This delays the possibility of treatment whereas early intervention improves treatment outcomes [9]. The distress and functional impairment caused by eating disorders, together with eating disorders correlation with depression, anxiety, substance use disorders and elevated risks of suicide attempts, reinforce the need of intervening with prevention interventions before eating disorder onset [1,10,11]. Moreover, there is a lack of treatment facilities providing specialised and evidence-based treatments for eating disorders [12], and evidence-based treatments do not suit every patient, with remission rates not superior to 50–60% of the patients with bulimia nervosa or binge eating disorder [13]. Finally, the costs generated by these disorders are underestimated; because they are not systematically declared, it is indeed difficult to have an objective view of the missed working days or of the complications that they cause. The critical period during which eating disorders develop, the difficulty of treating these disorders, the suffering they cause, together with the costs they generate, highlight their public-health significance, and lead researchers to recommand the development and evaluation of prevention interventions for eating disorders targeting young adults [14].

The prevention interventions built on the Dual Pathway Model [15] as theoretical foundations are among the most effective [16,17]. Stice proposed this model after a meta-analysis of the risk factors leading to compulsive disorder type [18]. It includes two identified pathways leading to the development of compulsive eating disorders: 1) dieting and 2) negative affect (Fig 1), with body dissatisfaction as the necessary and common risk factor.

**Fig 1 pone.0259796.g001:**
[figure not shown]
Stice’s Dual Pathway Model.

Based on this model, Stice and colleagues conceptualised a prevention intervention that targets the internalisation of the societal beauty ideal of thinness (thin-ideal internalisation in the model in Fig 1) in order to intervene upstream of body dissatisfaction. This intervention, called “Body Project” (BP), was first evaluated in comparison with a control group without intervention, in female undergraduates aged 18–22, with body dissatisfaction (N = 30), in the United-States (US) [19]. Then, the BP was compared to a placebo intervention specially designed for the study: the “Healthy Weight Program” (HW) in US young women aged 17–29 with body dissatisfaction [20]. When the two interventions were compared, the BP participants showed significant decreases in thin-ideal internalization, body dissatisfaction, dieting, negative affect, and bulimic symptoms. In parallel, decreases in thin-ideal internalization was not observed the HW participants, however this placebo intervention produced significant improvements, albeit smaller, of the other outcomes variables. To clarify these unexpected findings, a four-armed study compared the two intervention programmes with an emotional writing condition and a control group without intervention and followed up for up to three years in 481 US adolescent girls [21,22]. The results were favourable to the BP and the HW compared to the two control conditions, with a reduction in the onset of eating disorders at three years of 60% for the BP and 61% for the HW.

Since then, these two prevention interventions have been evaluated in various contexts. The BP intervention provided greater decreases of eating disorders risk factors than a video-control condition, whether led by a clinician, peers or delivered by an Internet platform [23]. The peer-led version of the BP turned out to produce the greatest reduction of eating disorders onset after four years, compared to the other form of program delivery [24]. The BP intervention was evaluated in other cultural context than US, for example Brazil [25] and Sweden [26], with similar outcomes, and without the need for cultural adaptation [25]. The BP and the HW interventions were also adapted and proposed to women athletes [27]. Both interventions significantly decreased eating disorders risk factors in this population, and the qualitative results suggested the athletes seemed to prefer the HW intervention. The BP is the eating disorder prevention programme which has collected the largest number of multiple independent replications of trials assessing its efficacy and effectiveness in reducing eating disorder risk factors and symptoms [28]. Because of the strong empirical support garnered by the BP in the US, scholars have recommended the examination of its potential to reduce eating disorders onset in Europe as well, which is in need of efficacious eating disorder prevention intervention [29]. Replication trials to assess the effectiveness of the HW, which is the only programme who has successfully addressed the prevention of eating disorders and obesity, are also needed [29].

Most studies evaluated the BP and the HW interventions in a context of selective prevention, intended for people with risk factors. Therefore studies included young women with body dissatisfaction. The BP and the HW interventions are both aimed at older adolescents and young adults, typically students. Excessive concerns with body image and disturbed eating behaviours often appear in adolescence and usually have not been addressed due to many reasons, from a desire to manage the problem by oneself, to a lack of time, or a lack of availability of treatment facilities [30–32]. But when young people arrive at university or enter higher education, the stress due to academic competition, the new environment, and the empowerment that accompanies this new stage of life may increase already existing difficulties [33]. Therefore, young women who are at-risk because of body dissatisfaction could greatly benefit from targeted interventions.

To our knowledge, no study has been carried out in Switzerland to evaluate an intervention for the prevention of eating disorders. Public health in French-speaking Switzerland lacks programs based on evidence in this field. This protocol presents a preliminary study to evaluate the acceptability and the effectiveness of the BP and HW interventions for female students in French-speaking Switzerland. Both of them have produced significant effects. The BP have produced larger effects [21,22], however the HW might be better accepted by certain sub-groups, such as athletes [27]. This is why we are interested in both of them. The study is preliminary in the sense that we want to collect participants’ satisfaction with each of the two interventions in order to assess their acceptability. A French version of the BP already exists, but no studies has yet been published on its effectiveness. The HW program will be translated in French by us. The script will be first translated literally and then adapted according to the Swiss recommendations for a healthy nutrition and physical activity. However, the core of the intervention, which is to set small objectives to modify permanently one’s dietary intakes and physical activity in order to reach energy balance, and discuss their attainment in group, will be kept identical. Besides, the two interventions will be compared to a waiting list to assess the interventions effectiveness, with a power able to detect large effect size.

The goal of this study is to assess the following three hypotheses:

The acceptability of the two interventions, assessed by the number of sessions that the participants attend, their satisfaction with the intervention, and qualitative comments provided by the participants, will be good for both interventions;The two interventions BP and HW will improve body dissatisfaction (primary outcome) as well as thin-ideal internalisation, dietary restraint, negative affect, and eating disorder psychopathology (secondary outcomes), compared to a waiting list;The improvements observed in the intervention groups (BP and HW) will be maintained after one month of follow-up.

## Materials and methods

### Study design

To compare the BP and HW interventions to a waiting list, we plan to carry out a three-arm randomised controlled study, including female students from French-speaking Switzerland. We will recruit 90 participants over a 12-month period, starting in January 2021. Participants will be randomly assigned to one of the three arms of the study. Both interventions are composed of four weekly sessions and last one month. The waiting list duration will be set to one month in a parallel way. Participants will be evaluated before (T0) and after (T1) the interventions or the waiting list. The interventions are given to groups of six participants and will start each time a group is formed following randomisation. Following the interventions, the participants will have one month of follow-up without contact with the investigators before a final evaluation (T2). To maximise the feasibility of the study regarding funding and university calendar, participants in the waiting list group will receive the BP intervention following the one-month waiting period instead of waiting until the end of the follow-up assessments. They will be evaluated at the end of the intervention (T2). The procedure is described in Fig 2.

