### Participants

The target population of the study are female students from the University of Geneva and other French-speaking cantons, and the University of Applied Sciences and Arts Western Switzerland (HES-SO) aged 18 to 25, with body dissatisfaction and a BMI between 18.5 and 30 kg/m^2^. To recruit the participants, a brief video proposing to test an intervention to improve one’s body dissatisfaction will be posted on the universities’ social networks. Students’ associations will be harnessed to convey information on the study.

The inclusion criteria are as follows:

Female student;Aged between 18 and 25 years old;BMI between 18.5 and 30 kg/m^2^;French-speaking (or understands French sufficiently to participate in the intervention) and living in Switzerland for at least six months;Suffers from body dissatisfaction and obtains a score of at least 26 on the BSQ-8C [34], which represents a moderate concern with body image;Accepts the use of a collaborative platform to participate in the intervention group, which implies that her name may be revealed, and accepts that the sessions will be recorded.

The exclusion criteria are:

Eating disorder diagnosis declared according to the DSM-5 diagnostic criteria (past or current);Any diagnosis of mood disorder or anxiety disorder;Pregnancy.

These criteria will be assessed during a first meeting via a phone call or videoconference by one of the members of the project team. If the participant meets the inclusion criteria and shows interest, she will receive the information and consent forms by mail, to be signed and returned. The participants will never be met face to face.

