### Random allocation

After receiving the consent form, the participant will be randomised into one of the three study arms, with a 1: 1: 1 allocation ratio. Randomisation will be blocked to ensure that groups are of equal size and that groups of six participants for each arm are regularly formed. The blocks will be of variable size (3, 6, 9) to protect the concealment. There is no stratification. The randomisation sequence will be implemented in the REDCap software, so none of the team members will know in advance which arm the next participant will be assigned to.

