### Blinding

The participants or the people performing the interventions will not be blinded to their conditions. In order to minimise bias, the main statistical analyses aimed at evaluating the hypotheses will be performed by a statistician who is blinded to the participants’ allocation.

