### Measures

Participants will complete the following questionnaires before the interventions or the waiting list (T0), after the interventions or the waiting list (T1), and after one month of follow-up or intervention (T2).

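### Women are randomised singly and openly, programmes start only once six have gathered, and nothing secures T0 before the arm is known: the baseline may follow allocation by weeks.

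*Protocol article*

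**What the plan says.** All references are to the Protocol article, Materials and methods.

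- **Trigger for randomisation (Random allocation).** The rule reads: "After receiving the consent form, the participant will be randomised into one of the three study arms, with a 1: 1: 1 allocation ratio". The sequence sits in REDCap in blocks of 3, 6 or 9, and the team does not know the next assignment. Entry is therefore one woman at a time. The same section says that groups of six are to be formed in each arm.
- **Start of the programmes (Study design).** "The interventions are given to groups of six participants and will start each time a group is formed following randomisation".
- **Waiting list (Study design, Interventions).** "The waiting list duration will be set to one month in a parallel way". The Interventions section puts its two assessments one month apart. Its members then receive BP, which is also delivered in groups of six.
- **Baseline (Measures).** "Participants will complete the following questionnaires before the interventions or the waiting list (T0"), with T1 after the programme or wait. T0 is not placed relative to randomisation or to disclosure of the arm.
- **Blinding.** "The participants or the people performing the interventions will not be blinded to their conditions".
- **Use of T0 (Data management and statistical analysis).** The pre score is the covariate in the ANCOVA comparing BP, HW and waiting list. The primary outcome, BSQ-8C, is a self-report questionnaire.
- **Selection (Participants).** A woman enters if she "obtains a score of at least 26 on the BSQ-8C".
- **Accrual (Study design).** "We will recruit 90 participants over a 12-month period, starting in January 2021".

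**The concern.** Each of these rules is reasonable alone. The difficulty is their order: allocate first, gather six afterwards, and measure baseline at a point fixed only by the start of the programme or wait.

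Hypothesis 2 is a controlled pre-post comparison with the waiting list. The waiting list removes natural course, academic-calendar effects and regression to the mean, the last of which is to be expected in a sample selected on a high score. It does this cleanly under two conditions: T0-T1 covers the same length of time in all arms, and T0 is not influenced by allocation. The stated sequence secures the two together only if the arm is withheld until T0, and no section provides for that.

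At stake are the covariate in the primary analysis, which could shift with anticipation or disappointment once the arm is known, and the intent-to-treat set. A woman who leaves between allocation and a late T0 contributes no questionnaire data, and such losses can differ by arm.

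**Working it through.** **1. Wait for a group, from the plan's own figures**

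- Accrual: 90 / 12 = 7.5 women per month. At 1:1:1 this is 7.5 / 3 = 2.5 per arm per month, a gap of 1 / 2.5 = 0.4 month between entries to one arm.
- Accrual time represented by one group: 6 / 2.5 = 2.4 months.
- Waits of the six members, first to last: 5, 4, 3, 2, 1, 0 times 0.4 = 2.0, 1.6, 1.2, 0.8, 0.4, 0 months.
- Mean: 6.0 / 6 = 1.0 month.

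Simulation with random arrivals at 7.5 per month and random blocks of 3, 6 and 9 agrees: mean 1.0 month, first member 2.0 months, 47% waiting more than one month and 12% more than two.

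**2. Dependence on the accrual assumption**

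| 90 recruited in | Mean wait (months) | First member (months) |
|---|---|---|
| 12 months (plan) | 1.0 | 2.0 |
| 9 months | 0.74 | 1.5 |
| 6 months | 0.5 | 1.0 |
| 3 months | 0.25 | 0.5 |

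The wait shrinks with faster entry but does not vanish. Only the last member of each group has none.

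**3. What follows for T0**

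- *T0 just before the start, groups of six gathered in every arm.* This fits the text best. T0-T1 is about one month in all arms. T0 comes on average about a month after allocation, and the participant may already know her arm.
- *T0 just before session 1 in BP and HW, but at once on the waiting list.* Intervals still match, but the delay from allocation to T0 exists in two arms only.
- *T0 around consent or randomisation.* T0 can then be free of allocation, but active T0-T1 is the gathering wait plus one month: 1.0 + 1.0 = about 2 months on average, from about 1 month (last member) to about 3 (first member, 2.0 + 1.0). The waiting-list interval is one month.

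The waiting list has its own difficulty. Six women randomised over about two months cannot each begin a six-person BP group exactly one month after allocation. Either their clock is held until six are present, so that T0 follows allocation, or their real wait exceeds one month.

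**4. Illustration only, on outside assumptions**

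- *Unequal intervals.* Assume a population BSQ-8C mean of 20 to 24, SD 8 to 9, selection at 26 or above, and a retest correlation falling by 0.05 to 0.10 between one and two months. Extra regression = (fall in correlation) x (selected mean minus population mean). Lowest case (mean 24, SD 8): 0.05 x 7.7 = 0.4 points. Highest case (mean 20, SD 9): 0.10 x 11.4 = 1.1 points. Dividing by the T1 SD implied in each case gives 0.07 to 0.20 SD over the grid.
- *Baseline after allocation.* An assumed T0 shift of 0.2 SD with an assumed ANCOVA slope of 0.6 moves the adjusted contrast by 0.2 x 0.6 = 0.12 SD. The sign depends on which arm shifts and which way.

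None of these inputs is in the document.

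**The case against.** The best defence has four parts.

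- **The intervals probably match.** T0 is tied to the start of the programme or wait, the waiting month is meant to run in parallel, and groups of six are to be formed in each arm. This stands. A reader might infer that the active arms certainly have a longer T0-T1 interval. The text does not support that; it is the less likely reading.
- **The arm could be withheld until T0.** Lack of blinding says nothing about when a woman is told. Sending T0 just before the start and disclosing the arm afterwards contradicts no section. This also stands, so it would be too strong to say that no course under the protocol gives a clean comparison. But no section provides for it, and women must be scheduled into arm-specific groups after allocation.
- **The flowchart (Fig 2) or the full protocol may place T0.** Fig 2 is not available here. If it places T0 relative to randomisation, that by itself decides which of the two problems applies. The start rule and the randomisation trigger are stated in the article, so the point is how they combine, not an omitted detail.
- **The bias may be small or conservative.** A reader might take 0.07 to 0.20 SD, or 14 to 40% of the 0.50 planning effect, as an estimate of inflation in favour of the programmes. It is not one. Self-selected volunteers may regress towards a higher mean than the one assumed, which would make the figure too large. If anticipation lowers T0 in the active arms, or disappointment raises it on the waiting list, the adjustment works against the programmes.

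The study also calls itself preliminary and able to detect only large effects. That tempers the consequence but does not remove the reason to fix the order of steps.

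**Conclusion.** The point holds as a flaw in the stated sequence. Individual open randomisation comes before the gathering of six, so there is an unblinded wait between allocation and programme start averaging about 1.0 month, and about 2.0 months for a group's first member. This assumes roughly even accrual of 90 women over 12 months.

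On the most natural reading the cost is a self-reported ANCOVA covariate collected after allocation, plus possible arm-dependent loss before any measurement. On the alternative reading it is an active T0-T1 interval of about two months against one. Size and direction of the bias cannot be derived from the document, and the SD-scale figures above are illustrations. Analysis cannot fully repair either problem afterwards, whereas the order of steps is cheap to change beforehand.

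**What to change.** **Preferred.** Randomise in batches:

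1. Accumulate 18 eligible, consented students.
2. Record T0 for all 18 in the week before the planned start.
3. Only then release a 6:6:6 allocation in REDCap.
4. Start BP, HW and the waiting month on the same date, and collect T1 on the same date in all three arms.

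Five batches give 5 x 18 = 90. In Study design, amend the rule that groups form after randomisation; in Random allocation, replace the single-entry blocks of 3, 6 and 9.

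**Minimum.** Set REDCap to release the arm only after T0 is recorded, take T0 at a common start date, and apply the same T0-T1 interval in all three arms.

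**Cost.** Protocol wording and REDCap set-up. Filling six places per arm already needs about 18 recruits, and 18 / 7.5 = 2.4 months is the same accrual time as one group now. The mean wait within a batch would be (17 / 2) / 7.5 = about 1.1 months, close to the present 1.0. Some recruits may be lost while a batch fills and will need replacing, which may take some time. That loss falls before randomisation and does not bias the comparison.
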